### Recruitment {15}

Patients will be recruited at the point of referral from the Long Covid Assessment Service into the Long Covid Rehabilitation Service. This referral is only completed when the assessing clinician has deemed them ready and clinically suitable for a rehabilitation programme.

Potential participants may be directly issued a patient information sheet (PIS) by their clinical team and asked if a member of the study team can contact them to discuss the trial either over the phone or via email (as per their preference). Patients invited at the point of referral will use the reply slip on the foot of the PIS and the included prepaid envelope to indicate they wish to be contacted by the study team. Potential participants that self-identify or are referred by their GP will be investigated and, if appropriate, invited to the Long Covid clinic prior to the commencement of the trial.

Personal information will not be accessed or reviewed by the study team until consent to contact has been obtained.

### Randomisation {16a, 16b and 16c}

Due to the sample size, stratification will be used to provide additional assurance that important factors are equally represented in the two trial groups to facilitate comparability [47]. The covariates deemed important in this case to balance are those of sex and age.

Randomisation will be generated through online randomisation software ‘Sealed Envelope’ (https://www.sealedenvelope.com), using block randomisation with stratified blocks of six participants. Researchers involved in delivering the rehabilitation programmes will implement the randomisation on ‘Sealed Envelope’ and assign participants. Individuals who are able to participate will be randomised on a 1:1 ratio to face-to-face rehab (intervention) or control (usual care).

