### Blinding {17a and 17b}

The statistician will be blinded, and blinded members of the research team will conduct post-intervention assessments. Due to the nature of the intervention, blinding the patient and wider intervention team will not be possible. The study co-ordinator will conduct baseline assessments and attend the rehabilitation class and therefore will not be blinded. Unblinding may be permissible in the interest of patient safety if there is an adverse event.

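### One published block size of six, with allocation run by the staff who deliver rehabilitation, lets about a fifth of allocations be deduced if those staff keep a tally by stratum

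*Protocol article*

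**What the plan says.** The Protocol article, section Randomisation {16a, 16b and 16c}, uses the online service Sealed Envelope, "using block randomisation with stratified blocks of six participants", with a 1:1 ratio. On stratification it says: "The covariates deemed important in this case to balance are those of sex and age". It gives no age bands, so the number of strata is unknown. It gives one block size and mentions no variation. On who operates the system: "Researchers involved in delivering the rehabilitation programmes will implement the randomisation on ‘Sealed Envelope’ and assign participants".

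The section Blinding {17a and 17b} says that "blinding the patient and wider intervention team will not be possible". It adds: "The study co-ordinator will conduct baseline assessments and attend the rehabilitation class and therefore will not be blinded". At the other end of the trial: "The statistician will be blinded, and blinded members of the research team will conduct post-intervention assessments".

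The section Trial design and setting {8 and 9} describes a single-centre exploratory trial. Sample size {14} sets recruitment at 56. Trial status gives a recruitment start of November 2024 and an estimated end of December 2025.

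**The concern.** Concealing the list protects the next allocation only if it cannot be inferred from earlier ones. With a constant block of six at 1:1, once one arm has had three places in the current block, the rest of that block is known. Inference needs the block size, the running count in the stratum and sight of past allocations. The first is published. The other two are within reach of staff who make the allocations and see who attends the classes.

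Two things are at stake. The first is selection: entry involves judgement (symptoms that rehabilitation might modify, the severity of fatigue), so knowing the next arm could affect whether or when a patient is enrolled. The second is the baseline incremental shuttle walk test (ISWT). The primary outcome is absolute change in ISWT distance, so a metre gained or lost at baseline passes metre for metre into that participant's change. The baseline assessor is the unblinded co-ordinator.

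**Working it through.** The plan states no predictability figure, so there is none to reproduce.

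**Inputs.** Block size 6 and ratio 1:1, so three places per arm (Randomisation). 56 participants (Sample size). Strata from sex and age: the age bands are not given, so I assume two bands and hence four strata, and show one to eight. Condition for all figures: someone knows the block size and keeps the count within each stratum.

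**Step 1: one complete block.** There are C(6,3) = 20 equally likely orders. An allocation is certain when one arm has already used its three places.

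- Places 1 to 3: never certain.
- Place 4: the first three are all the same arm, 2/20 = 0.10.
- Place 5: the first four contain three of one arm, 2 × C(4,3)/20 = 8/20 = 0.40.
- Place 6: always certain, 1.00.

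The sum is 0.10 + 0.40 + 1.00 = 1.5 of 6, or 25%. The closed form agrees: 2m/(m+1) with m = 3 gives 6/4 = 1.5.

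**Step 2: this trial.** Unfinished blocks contribute mainly early places, which are rarely certain, so the expected share falls below 25%.

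- One stratum: 56 = 9 × 6 + 2, so 9 × 1.5 = 13.5, and 13.5/56 = 24.1%.
- Four strata of 14: each has two complete blocks plus two, so 2 × 1.5 = 3 each, 12 in all, and 12/56 = 21.4%.
- With stratum sizes left to chance (simulated): 23.1% for two strata, 21.3% for four, about 19% for six and 18% for eight.

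With four strata, the share realised in a single trial has a 95% range of 14% to 29%, that is 8 to 16 of 56.

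**Step 3: guessing.** Guessing the arm that is behind in the block, with a coin toss when level, is right in 4.1 of 6 places (68.3%) in complete blocks. It is right in about 67% with 56 participants in four strata, against 50% with no information.

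**Step 4: randomly varying sizes.** Simulated with 56 participants and four strata, for a guesser who knows the set of sizes but not their order:

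| Block sizes | Certain in advance | Best guess correct |
|---|---|---|
| 6, fixed | 21% | 67% |
| 4 and 6 | 6.0% | 68% |
| 2, 4 and 6 | 3.5% | 69% |
| 4, 6 and 8 | 2.4% | 66% |

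Varying the sizes removes most of the certainty. It does not reduce the advantage of an informed guess to any useful extent.

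**The case against.** The case on the other side has real substance.

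- **Tracking is not documented.** The article says researchers, in the plural, run the allocation. It does not say that any one of them sees every allocation by stratum, nor that the co-ordinator allocates. A reader might infer that delivery staff do know upcoming allocations; the text shows only that they could work them out. This stands, so every figure above is conditional.
- **A quarter is too high.** A reader might take 25% as the trial's figure. It applies to complete blocks, and every expected value computed here for 56 participants is below it. This stands.
- **Entry is partly outside the study team's hands.** Under Recruitment {15}, referral depends on the assessing clinician's judgement of suitability, and the study team sees no personal information before consent to contact. This narrows the scope for selection. It does not close it, because members of the study team take consent.
- **The test is constrained.** The ISWT is paced by audio signals, follows technical standards and is done twice at baseline. That limits differential encouragement without excluding it, since the assessor can end the test.
- **Follow-up assessors and the statistician are blinded.** This protects the second measurement, but not enrolment or baseline.
- **No bias has been sized.** A reader might conclude that the treatment comparison will be biased beyond repair. The percentages measure predictability. The documents give neither a direction nor a size for any effect on the ISWT difference, so that conclusion is unsupported.

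The SPIRIT table puts allocation and baseline tests in one enrolment column, and a reader might infer that allocation comes first. The table does not fix the order, the flow chart is not shown, and such detail is commonly left to the full protocol. No finding rests on it.

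**Conclusion.** The concern holds as a conditional weakness in allocation concealment that is cheap to reduce. It rests on stated choices: one constant, published block size, one centre, visible arms, and allocation by those who deliver the intervention. If those staff count within strata, about 12 of 56 allocations (21%) can be deduced with certainty under four assumed strata. What follows is an opening for selection and for influence on baseline ISWT, limited by the referral route and the paced test. It is not evidence that either has occurred.

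**What to change.** For all remaining randomisations, have Sealed Envelope draw block sizes at random, for example from 4, 6 and 8 or from 2, 4 and 6, and do not disclose them to recruiting or delivery staff. Certain allocations then fall to about 2% to 4% even if the set of sizes becomes known.

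Because informed guessing stays at about 66% to 69%, the change of block size should not be presented as a complete remedy. Where existing staffing allows, a team member with no part in recruitment, baseline testing or delivery should request each allocation.

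The cost is a configuration change in the service already in use and a short protocol amendment. The mid-trial change and its date must be documented. Closing a block of six early can leave a difference of up to three between arms in that stratum. The change helps only participants not yet randomised, and the article does not say how many those are. If none remain, report the fixed block size and the role of delivery staff in allocation as a limitation.

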### Blinding {17a and 17b}

The statistician will be blinded, and blinded members of the research team will conduct post-intervention assessments. Due to the nature of the intervention, blinding the patient and wider intervention team will not be possible. The study co-ordinator will conduct baseline assessments and attend the rehabilitation class and therefore will not be blinded. Unblinding may be permissible in the interest of patient safety if there is an adverse event.

### Data management {18a, 19, 27 and 29}

All investigators and study site staff will comply with the requirements of the Data Protection Act 1998 with regard to the collection, storage, processing, and disclosure of personal information. All trial documentation containing identifiable patient data will be managed in accordance with ICH GCP, the UK Policy Framework for Health and Social Care, and the 2018 UK General Data Protection Regulation (GDPR).

The trial personnel will ensure that the participants’ anonymity is maintained. Following consent, each participant will be given a unique participant identifier code to preserve the anonymity of the data.

Quantitative data will be entered into an electronic data capture tool (REDCap) hosted by the BRC. The minimum number of individuals necessary for quality control, audit, and analysis will be granted permission to use this data within the national safe haven. Data will be quality checked by a second researcher, and any outliers will be explored and removed as appropriate. Data validation will take place at the end of the study prior to data lock.

Confidentiality will be maintained for qualitative data, which will be anonymised at the point of transcription, the only reference on the recording being the unique participant identifier. All personal names, place names, and organisation names, and any other data deemed to risk potential identification of a participant, will be anonymised. Audio recordings will be stored securely with password encryption on the electronic site file; once transcriptions are finalised, the files will be deleted.

Only the CI, study coordinator, and statistician will have access to the full dataset. Other members of the research team and wider research community may make a formal data use request in writing to access the full dataset; however, any such requests must be approved by the Trial Management Group. Participating investigators have rights to publish discrete elements of the study data.

### Statistical analysis {20a, 20b and 20c}

The analysis will compare the intervention group to the usual care group. Changes in the primary outcome (ISWT distance) will be compared between the groups using a paired *t*-test (or nonparametric equivalent if the data is not normally distributed). Two sensitivity analyses will be conducted for the primary outcome: (1) Missing data will be imputed using multiple imputation allowing for a full ITT analysis and (2) a per-protocol analysis with those that adhere to the intervention defined if they attended 75% of face-to-face sessions or attended for follow-up appointments.The ISWT will also be analysed using generalised linear mixed models (GLMM); this will allow for in-group adjustments for other variables which may add to the richness of the qualitative data at the point of data mixing.

Secondary outcomes are not powered. All analysis of the primary and secondary outcomes will be performed using R (Version 4.3.1), [48]. Continuous variables will be analysed using the *t*-test or nonparametric equivalent. Categorical variables will be analysed using the chi-squared test or non-parametric equivalent.

Blood biomarkers will be analysed using generalised linear mixed models (GLMM) or similar, with intervention group (control vs face to face), time point (pre vs post), and group × time treated as fixed effects; a random intercept will be included for the participant identifier, and all models will be adjusted for sex and baseline values for each variable.

For the heart rate variability, data will be analysed using robust signal processing approaches by a research associate. Advanced HRV analysis will be performed with the Holter ECGs. Biomarkers of interest include QT variability, signal averaging ECG (fragmented QRS complexes), temporal T-wave morphology variability, and T-wave alternans. These features will be compared and combined to be further correlated with patient-specific characteristics.

GLMMs will be fitted using the lmer function from the lme4 package [49]. Missing data for the primary and secondary outcomes will be imputed using a Bayesian framework. GLMMs will be fitted to outcomes with and without imputation. Imputation was performed using the JointAI library [50].

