#### Primary outcome

Maximal exercise capacity was measured by absolute change in ISWT distance (in metres) 6 weeks after baseline (±2 weeks). The ISWT will be performed in line with technical standards [32]. In brief, the test is an externally paced, incremental test that requires the patient to walk around a 10-m (m) course at a target speed dictated by audio bleeps. As a maximal, progressive test, the walking speed starts slowly but increases each minute, with the test terminated when the patient is no longer able to keep up with audio cues or by the assessor if the required speed is not attained. The test will be performed twice pre-intervention for familiarisation, with the highest distance achieved used for exercise prescription (ESWT speed). The test will be repeated once after the intervention (Table 1).

**Table 1 Tab1:** Secondary outcome measures

Acceptability	Physical Measures	Questionnaires
Quantitative measure of completion in the intervention group	Short physical performance battery (SPPB) [33]	Generic HRQoL: EQ-5D-5L [34]
Qualitative evidence via focus groups and semi-structured interviews	Physical activity monitoring: ActiGraph accelerometer device [35]	Fatigue: Functional Assessment of Chronic Illness Therapy Fatigue Scale (FACIT-Fatigue) [36]
	Maximum isometric quadriceps strength (kg) [37]	Depression: Patient Health Questionnaire (PHQ9) [38]
	Endurance Shuttle Walk Test (ESWT) (seconds) [39]	Anxiety: Generalised Anxiety Disorder 7-item scale (GAD7) [40]
		Breathlessness: MRC Dyspnoea scale [41]
		Covid-specific HRQoL: Modified C19-YRS [42]
		Cognitive Function: Montreal Cognitive Assessment (MoCA) [43]
		Post Exertional Malaise: DePaul Symptom Questionnaire Short Form (DSQ-SF) [25]

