### Sample size {14}

The sample size for the randomised controlled trial is calculated based on the primary outcome of ISWT distance, with a change of 50 m at 90% power, a standard deviation of 17 m, and 0.05 type 1 error. These figures have been previously determined and referenced in the literature as the minimum important difference and variance for the ISWT [10, 45].

The sample size required is based on a power calculation for a two-sample *t*-test. The pwr.t.test function from the pwr package [46], in R, was used to calculate a required sample size of 23 participants per group, 46 participants in total. This has been inflated by 20% to allow for attrition, and, therefore, 56 participants will be recruited.

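### The primary test is named as a paired t-test, but the arms are independent and unmatched and the sample size rests on a two-sample t-test

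*Protocol article*

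**What the plan says.** All references are to the protocol article.

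- **Statistical analysis {20a, 20b and 20c}** states the aim: "The analysis will compare the intervention group to the usual care group". It then names the primary test: "Changes in the primary outcome (ISWT distance) will be compared between the groups using a paired" t-test, with a nonparametric equivalent if the data are not normal. Multiple imputation and a per-protocol analysis follow as sensitivity analyses, and a mixed model for the ISWT as a further analysis. Continuous variables in general get a t-test of unstated type.
- **Sample size {14}**: "The sample size required is based on a power calculation for a two-sample" t-test, giving 23 per group, 46 in total, and 56 after allowance for attrition.
- **Randomisation {16a, 16b and 16c}**: participants "will be randomised on a 1:1 ratio to face-to-face rehab (intervention) or control (usual care"), "using block randomisation with stratified blocks of six participants". Stratification is by sex and age. No participant is matched to another.
- **Primary outcome**: "absolute change in ISWT distance (in metres) 6 weeks after baseline (±2 weeks"), which is one change score per participant.

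**The concern.** A paired t-test needs a defined link between each observation in one set and one observation in the other. Within a participant, baseline and follow-up are linked. Between the arms nothing is linked, because stratified blocks balance group totals but do not create couples. The sentence therefore joins a between-group aim to a test that cannot serve it. The fallback inherits the fault: the nonparametric counterpart of a paired t-test is the signed-rank test, whereas independent arms need a rank-sum procedure.

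This is the primary analysis of the primary outcome. Left as it stands, the analyst must either follow a test that does not fit the design or depart from the published plan once data are in hand. A within-arm before-and-after test would also leave natural recovery mixed with treatment benefit. The Background raises that problem about earlier studies, most of which were observational cohorts.

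**Working it through.** **1. The plan's own figure.** The inputs in Sample size are: "with a change of 50 m at 90% power, a standard deviation of 17 m, and 0.05 type 1 error". The standardised difference is 50/17 = 2.94. A two-sided two-sample t-test at 0.05 then reaches 93.0% power with 4 per group, so 23 per group is not reproduced. A paired calculation with the same inputs needs 4 pairs (96.2% power), so reading the calculation as paired does not yield 23 either. With 23 per group, 90% power corresponds to a standardised difference of 0.977, that is, an SD of 50/0.977 ≈ 51 m. The inflation does reproduce: 46 × 1.20 = 55.2, rounded up to 56 for two equal arms. The mismatch with 17 m is a separate matter. Here it matters only that correcting the name of the test does not alter 23, 46 or 56, since they are already declared as a two-sample result.

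**2. Literal reading: pairing across arms.**

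- *Unequal arms.* The test is undefined; a trial run with 23 and 22 values returned an error. Equal arms cannot be counted on. The plan allows for 20% attrition, and 56 is not a multiple of the block size of six (9 × 6 = 54), so at least one block will be incomplete.
- *Equal arms, arbitrary pairs.* Let σ be the SD of change. The difference between two unrelated participants has SD σ√2, so the standardised effect becomes d/√2. With d = 0.977 and n = 23:
  - paired: noncentrality (0.977/√2) × √23 = 3.31, 22 df, critical t 2.074, power **88.6%**;
  - two-sample: noncentrality 0.977 × √(23/2) = 3.31, 44 df, critical t 2.015, power **90.0%**.
- *Type I error.* In 20,000 simulated trials with no effect, arbitrary pairing rejected in 5.0%, as did the two-sample test.

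The noncentrality is the same for both; only the degrees of freedom differ. The remaining cost is that the p-value changes with the order in which participants happen to be listed, and that unmatched participants may be dropped.

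**3. Alternative reading: before versus after within each arm.** Suppose there is no true treatment effect and both arms improve by the same mean m. In an arm of 23, the chance p of a significant paired test follows from the noncentral t with noncentrality √23 × m/σ on 22 df. The arms are independent, so the pattern of rehabilitation significant and control not has probability p(1 − p), which can never exceed 25%. The values of m are assumptions. An SD of change of 50 m is also an assumption, close to the 51 m in step 1; 17 m is the only SD that the protocol states.

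| Common improvement m | p, SD 50 m | p(1 − p), SD 50 m | p, SD 17 m | p(1 − p), SD 17 m |
|---|---|---|---|---|
| 5 m | 7% | 7% | 27% | 20% |
| 10 m | 15% | 13% | 77% | 18% |
| 15 m | 28% | 20% | 98% | 2% |
| 20 m | 45% | 25% | >99.9% | about 0% |
| 25 m | 63% | 23% | >99.9% | about 0% |
| 30 m | 79% | 17% | >99.9% | about 0% |
| 40 m | 96% | 4% | – | – |
| 50 m | 99.6% | 0.4% | – | – |

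The misleading pattern thus ranges from about 0% to 25%. Where it is rare at large m, the reason is that both arms test significant, which again says nothing about the treatment contrast.

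**The case against.** The strongest reply is that this is a slip in one word. The sentence itself says that changes are compared between the groups, the sentence before it names the two groups, the endpoint is one change score per participant, and the sample size uses a two-sample test. All of this points to an independent comparison of change scores; the word paired may only echo the within-person subtraction. That is a fair account of the likely intent, and it limits the consequence. It does not remove the contradiction, because nothing in the document corrects the named test.

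A reader might infer more: that the trial will test each arm before versus after, with a false-positive rate near 25%. The document does not support this. No section describes a within-arm primary test, and 25% is the ceiling of p(1 − p), reached only for particular assumed values of improvement and SD. A reader might also blame walking-test learning for a spurious gain. The Primary outcome section schedules two baseline tests for familiarisation, which reduces that effect though it may not abolish it, so the point should not lean on it.

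The planned mixed model means that the paired test is not the only ISWT analysis. It is an additional analysis, however, and does not replace the primary test.

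**Conclusion.** The point stands as an error of specification and an internal contradiction: the stated primary test does not fit two independent, unmatched arms and differs from the test used for the sample size. Its fallback is wrong for the same reason.

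The size depends on how the sentence is carried out. Paired literally across equal arms, the loss is about 1.4 percentage points of power (90.0% to 88.6%, at 23 per arm and the effect size that gives 90%), with type I error near 5% and a result tied to an arbitrary order. With unequal arms there is no result. Run within arms, the test misses the randomised contrast, and the misleading pattern occurs in roughly 0–25% of null trials. That range assumes 23 per arm, normally distributed changes, and the same mean and SD of change in both arms. It is conditional on a use that the text does not describe.

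The correction is needed despite the modest damage under the literal reading, because it concerns the primary analysis and the repair is trivial.

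**What to change.** In Statistical analysis, replace the paired t-test with an independent two-sample comparison of change in ISWT distance between the arms, reporting the mean difference and its 95% CI. A baseline-adjusted model would also be acceptable. Name the nonparametric fallback as a two-independent-sample procedure (rank-sum). Check that Sample size and Statistical analysis then name the same comparison.

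The cost is one sentence, recorded as a protocol amendment and carried into any analysis plan before data lock. It does not change recruitment, visits, data collection or the stated 23, 46 and 56.

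### The primary test of ISWT change adjusts for neither baseline ISWT nor the stratification factors, and lets the data choose the test: valid, but less efficient than it could be and not fully fixed in advance

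*Protocol article*

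**What the plan says.** All references are to the protocol article.

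- **Statistical analysis, primary test:** "Changes in the primary outcome (ISWT distance) will be compared between the groups using a paired" t-test, or a "nonparametric equivalent if the data is not normally distributed". No covariate is named and no criterion for non-normality is given. The two sensitivity analyses (multiple imputation and per-protocol) deal with missing data and adherence; neither is said to add adjustment.
- **Statistical analysis, supplementary model:** "The ISWT will also be analysed using generalised linear mixed models (GLMM); this will allow for in-group adjustments for other variables". The variables are not named, and the stated purpose is to enrich the qualitative data when the two strands are mixed. A later sentence has GLMMs fitted to outcomes with and without imputation. By contrast, the blood biomarker models are stated to adjust for sex and for the baseline value.
- **Randomisation:** "The covariates deemed important in this case to balance are those of sex and age".
- **Primary outcome:** "absolute change in ISWT distance (in metres) 6 weeks after baseline". The ISWT is performed twice before the intervention, so the baseline covariate is already collected.
- **Sample size:** "with a change of 50 m at 90% power, a standard deviation of 17 m, and 0.05 type 1 error"; "The sample size required is based on a power calculation for a two-sample" t-test, which "was used to calculate a required sample size of 23 participants per group, 46 participants in total".

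**The concern.** Sex and age are treated as important enough to stratify on, and baseline ISWT is available for everyone, but none of the three is a covariate in the analysis that answers the primary objective. Three things follow.

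1. A change score fixes the coefficient on baseline at 1. Regression to the mean makes the best coefficient smaller unless the two measurements are very highly correlated, so some chance baseline imbalance stays in the estimate and some precision is lost.
2. Stratified randomisation removes between-stratum variation from the treatment contrast. An analysis that leaves the strata out keeps that variation in the standard error, which is then too large if sex and age predict change.
3. If the trial's own data decide between a t-test and a rank test, it is not settled beforehand whether the primary result is a difference in mean change, which can be set against 50 m, or a rank-based quantity.

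The primary test is fixed by the protocol, so this is not a detail left to the analysis plan: an analysis plan that named ANCOVA as primary would contradict it. The Abstract expects recruitment to be difficult, so precision has value here.

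**Working it through.** **Inputs from the protocol:** difference 50 m, SD 17 m, power 90%, alpha 0.05 (two-sided assumed), 23 per arm, 1:1 allocation, 56 recruited. **Not in the protocol, so assumed:** the baseline to follow-up correlation (rho), a realistic SD of change, and the share of variance in change explained by sex and age. The test is taken as two-sample, as under Sample size; the word paired does not fit a between-group comparison and is a separate point.

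**1. The plan's own figure.** The standardised difference is 50/17 = 2.94. A two-sample t-test then needs 4 per arm (power 93%; 3 per arm gives 77%), so 23 per arm does not reproduce. Solving for 23 per arm at 90% power gives a standardised difference of 0.977, that is an SD of 50/0.977 = 51.2 m. The 17 m is therefore not usable for judging precision. About 51 m is the value that the stated sample size implies.

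**2. ANCOVA against change score.** With equal SD s at both visits:

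- variance of change = 2s²(1 − rho)
- residual variance after regression on baseline = s²(1 − rho²)
- ratio = (1 − rho²) / [2(1 − rho)] = (1 + rho)/2

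Two-sample t-test power with 23 per arm and 50 m, before any loss of degrees of freedom:

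| rho | Variance ratio | CI width ratio | Power, SD of change 51.2 m | Power, SD of change 60 m (assumed) |
|---|---|---|---|---|
| change score | 1 | 1 | 90% | 79% |
| 0.5 | 0.75 | 0.866 | 96% | 89% |
| 0.7 | 0.85 | 0.922 | 94% | 85% |
| 0.8 | 0.90 | 0.949 | 93% | 83% |
| 0.9 | 0.95 | 0.975 | 91% | 81% |

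At the stated SD of 17 m, power is above 99.99% with or without adjustment.

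**3. Counting the degrees of freedom.** This simulation used 5,000 runs, 23 per arm and an SD of change of 51.2 m, with baseline, sex and age group in the model and sex and age given no prognostic value, so that they only cost degrees of freedom. Power for ANCOVA against the change t-test was:

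- rho 0.5: 95.2% against 89.6%
- rho 0.7: 92.8% against 89.7%
- rho 0.8: 90.9% against 89.9%
- rho 0.9: 89.5% against 89.9%

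**4. Leaving out the strata.** The relevant R² is the share of variance in change, not in walking distance. Under perfect balance the true size of the unadjusted test is 2[1 − Φ(1.96/√(1 − R²))], which is 3.9%, 2.8% and 1.9% for R² of 0.1, 0.2 and 0.3. Incomplete blocks and attrition weaken this. Simulations with 56 randomised in stratified blocks of six, four sex-by-age strata (assumed) and about 46 analysed gave 4.1–4.4%, 3.1–3.3% and 2.4–2.8%.

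**5. The normality switch.** This simulation used 5,000 runs and 23 per arm, choosing between the t-test and Mann-Whitney by Shapiro-Wilk in each arm (the protocol names no criterion, so this is assumed). Rejection under the null was 5.4% with normal data and 4.9% with skewed data, within simulation error of 5%. With normal data the switch was triggered in about 10% of trials.

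**The case against.** The strongest case on the other side is that nothing here is invalid. Several stronger readings are tempting, and the documents do not support them.

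- **That the analysis ignores baseline ISWT or is biased.** A change score uses baseline by subtraction, and under randomisation its contrast is unbiased. Only covariate adjustment is missing. The unadjusted test also matches the test used for the sample size.
- **That a sizeable gain is assured.** The protocol gives no rho. If sex and age do not predict change, the gain is about one percentage point of power at rho 0.8 and nil at 0.9. A high rho cannot be excluded: with an SD of change of 51.2 m, rho 0.5 means a cross-sectional SD of only 51.2 m, and rho 0.9 means 114.5 m, in a population of adults over 18 with no upper age limit.
- **That omitting the strata risks false positives.** The error runs the other way; the test is conservative. Stable differences in walking distance by sex and age cancel on subtraction, so an R² of 10–30% for change is only an assumption.
- **That the switch inflates type I error or leaves no result in metres.** The simulation shows no inflation. A rank test can carry a location-shift estimate in metres, and the GLMM of ISWT is planned in any case. What stands is that the test and effect measure are not fixed beforehand.
- **That the GLMM already supplies the adjustment.** It is an additional analysis with unnamed covariates and a stated role in the qualitative integration. An analysis plan might name the covariates, but that would not make it the primary analysis. This narrows the point without removing it.

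The trial also calls itself exploratory, which tempers the urgency.

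**Conclusion.** The point holds as one of efficiency and pre-specification, not of validity. The protocol fixes an unadjusted primary comparison although the prognostic baseline measure and both stratification factors are to hand, and it leaves the choice of test to the data.

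For rho between 0.5 and 0.9, ANCOVA has 25% to 5% less variance than the change score, so a confidence interval about 13% to 2.5% narrower. Whether that matters for power depends on the SD of change: worthwhile at about 51 m or 60 m when rho is 0.5 to 0.7, small from 0.8 upward unless sex and age predict change, and irrelevant if 17 m were right. Omitting the strata makes the test conservative, at roughly 4% to 2.5% instead of 5% for an assumed 10–30% of the variance in change.

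Confidence is high in what the plan says and in the direction of the effect, and lower in its size, because rho, the SD of change and the R² are all assumed. The change should be made because it costs almost nothing.

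**What to change.** Amend Statistical analysis as follows.

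- Make the single primary analysis a linear regression (ANCOVA) of 6-week ISWT distance on arm, baseline ISWT, sex and age, with age continuous or as stratified. Use the same baseline value that the change score would subtract.
- Report the adjusted mean difference in metres with its 95% confidence interval, to be read against 50 m.
- Remove the normality switch. Deal with non-normality by robust (HC3) or bootstrap intervals, and keep a rank test as a sensitivity analysis only.
- Use the same model for continuous secondary outcomes, with each outcome's own baseline.
- Label the GLMM as supportive and name its covariates.

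The cost is wording, plus about three residual degrees of freedom. No new data, visits or participants are needed. The same sentence has to be revised anyway, because its paired t-test conflicts with the two-sample test under Sample size.
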